## Abstract

**Background:**

Sepsis is associated with about 20% of deaths worldwide. It often presents with non-specific initial symptoms, making its emergency treatment an interdisciplinary and cross-sectoral challenge. Three in four sepsis survivors suffers from new cognitive, psychological, or physical sequelae for which specific treatment concepts are scarce. The AVENIR project aims to improve the understanding of patient pathways, and subjective care experiences and needs along the entire healthcare pathway before, with and after sepsis. Based on this, concrete recommendations for the organization of care and patient information materials will be developed with close patient participation.

**Methods:**

Mixed-methods study including (1) analysis of anonymized nationwide health claims data from Germany, (2) linkage of health claims data with patient care reports (PCR) of emergency medical services from study regions in two federal states within Germany, and (3) qualitative exploration of the patient, relative, and care provider perspective on sepsis care. In (1), we analyze inpatient and outpatient health care utilization until 30 days pre-sepsis; clinical sepsis care including intra- and inter-hospital transfers; and rehabilitation, inpatient and outpatient aftercare of sepsis survivors as well as costs for health care utilization until 24 months post-sepsis. We attempt to identify survivor classes with similar health care utilization by Latent Class Analyses. In (2), PCR are linked with health claims data to establish a comprehensive database outlining care pathways for sepsis patients from pre-hospital to follow-up. We investigate e.g., whether correct initial assessment is associated with acute (e.g., same-day lethality) and long-term (e.g., new need for care, long-term mortality) outcomes of patients. We compare the performance of sepsis-specific screening tools such as qSOFA, NEWS-2 or PRESEP in the pre-clinical setting. In (3), semi-structured interviews as well as synchronous and asynchronous online focus groups are conducted and analyzed using qualitative content analyses techniques.

**Discussion:**

The results of the AVENIR study will contribute to a deeper understanding of sepsis care pathways in Germany. They may serve as a base for improvements and innovations in sepsis care, that in the long-term can contribute to reduce the personal, medical, and societal burden of sepsis and its sepsis sequelae.

**Trial registration:**

Registered at German Clinical Trial Register (ID: DRKS00031302, date of registration: 5th May 2023).

## Background

Sepsis is the most serious complication of infectious diseases, in which organ failure and shock occur due to a dysregulated immune response of the body to any bacterial, viral, fungal or parasitic infection [1]. Annually, an estimated 49 million patients develop sepsis globally, of which 11 million die [2]. In Germany, approximately 150,000 patients were hospitalized with sepsis in 2016; the in-hospital case fatality was 40% [3]. In the long-term, three out of four sepsis survivors suffer from new-onset physical, psychological, and/or cognitive sequelae in the year post-sepsis. These symptoms are summarized as Post-Sepsis Syndrome (PSS) [4] and include neuromuscular, cardiovascular, and urogenital disorders as well as depression, fatigue, and cognitive impairment [5]. Given the large number of possible (severe) sequelae, a high proportion of sepsis survivors is rehospitalized after recovering from the initial septic insult, often for re-emerging infections, sepsis and cardiovascular disease [6, 7]. Of these rehospitalizations, 22% occurred with so-called ambulatory-care sensitive diagnoses according to an US-study [6], many of which are considered potentially preventable, for example, through vaccination [6]. The costs incurred by acute treatment and long-term care of those suffering from sepsis annually in Germany up to three years after the index illness amount to approximately 12 billion Euro, making sepsis acute and long-term care a medical and societal challenge [4].

To a high-quality acute and long-term sepsis care, however, there are numerous challenges. First, given its non-specific early symptoms, sepsis is often recognized and treated with delay, [8] resulting in a considerable number of preventable deaths. Second, a multitude of disciplines are involved in pre-clinical, acute, and post-acute sepsis care, which increases the risk of delays and loss of information [9]. Third, for the large number of sepsis survivors with sequelae, there is a lack of widely available and effective aftercare options that can address the diverse spectrum of physical, cognitive, and psychological sequelae [10]. This may be one of the reasons why only a small proportion of sepsis patients (17%) receive rehabilitation after their acute care hospitalization in Germany [11]. A survey among sepsis survivors also revealed that such rehabilitation often addresses only a small proportion of the sequelae [12]. Specific rehabilitation concepts for sepsis survivors are lacking, and survivors call for better and more specific follow-up care [13].

In view of these deficiencies in care, the WHO called on its member states in 2017 to improve the prevention, diagnosis, and adequate treatment of sepsis and its consequences [14]. A prerequisite for the development and implementation of effective care strategies, however, is the improved understanding of care pathways and experiences of sepsis patients, which have been insufficiently studied to date. The AVENIR project therefore aims to (i) analyze care pathways of patients with and after sepsis in the German health care system, (ii) identify patient classes with similar patterns of health care utilization after sepsis and examine their association with sepsis, patient, and treatment characteristics, and (iii) describe subjective care experiences and needs of sepsis patients and health care providers. Based on this evidence, materials for patient information will be developed and concrete recommendations for the organization of health care will be derived.

## Methods/design

AVENIR is a mixed-method, non-interventional study, which consists of three modules (Fig. 1). The study was pre-registered in the German Clinical Trials Registry (ID: DRKS00031302).

**Fig. 1 Fig1:**
[figure not shown]
AVENIR modules by sepsis care pathway

### Module 1: Pre-clinical, acute and post-acute health care pathways—analysis of anonymized nationwide health claims data

#### Design and data source

In module 1, we perform a population-based observational cohort study using health claims data from eleven legally independent statutory health insurance funds of the ”AOK – Die Gesundheitskasse” (local health care funds) covering around one third of the German population. Enrolment into statutory health insurance is unrestricted regarding age, health status, income, employment, or geographical region. The routine data from 2015–2021 are provided by AOK Research Institute (WIdO), including a de-identified patient ID that allows for longitudinal analyses and linkage of data within the database. Administrative data for inpatient and outpatient care (§ 301 Social Code Book V (SGB V), §295 SGB V) as well as for rehabilitation therapies (§ 301 SGB V), outpatient medication (§ 300 SGB V), medical remedies (§ 302 SGB V), sickness benefits payments (§295 SGB V), care in disease management programs (§ 137f SGB V), home nursing care (§ 302 SGB V) and benefits of the statutory long-term care insurance according to SGB V and XI are analyzed.

#### Patient sample

Patients > 15 years of age with hospital-treated sepsis in 2016–2020 are included, as identified by the following strategies based on primary or secondary ICD-10-GM hospital discharge diagnoses (Table 1).

**Table 1 Tab1:** Sepsis definition criteria in health claims data

Year(s)	Sepsis and Infection ICD-10-GM Codes	Organ dysfunction ICD-10-GM or OPS Codes
2016–2019	R57.2 (septic shock) OR	
	R65.1 (severe sepsis) OR	
	At least one explicit sepsis code (A02.1, A20.0, A20.7, A21.7, A22.7, A24.1, A26.7, A28.2, A32.7, A39.1, A39.2, A39.3, A39.4, A40, A41, A42.7, A48.3, A49.9, A54.8, B00.7, B37.6, B37.7, B49, O75.3, O85, T80.2, T81.4, T88.0)	AND at least one ICD-10-GM code for organ dysfunction (J80.0, J95.1, J95.2, J96.0, J96.9, R09.2, D65, D69.57, D69.58, D69.59, D69.6, R57.8, E86, I95.9, I46.0, I46.9, R57.2, K72.0, K72.9, R17, N17.02, N17.03, N17.12, N17.13, N17.22, N17.23, N17.82, N17.83, N17.92, N17.93, F05, G94.32, K72.72!, K72.73!, K72.74!, R40, G93.4) OR OPS code for organ dysfunction (8–701,^a^ 8–704,^a^ 8–706,^a^ 5–311,^a^ 5–312,^a^ 8–800.6, 8–800.d, 8–800.f, 8–800.g, 8–800.h, 8–800.j, 8–800.k, 8–800.m, 8–800.n, 8–810.j, 8–810.x, 8 812.5, 8–812.6, 8–812.8, 8–771, 8–779, 8–852, 8–858, 8–821.2, 8–853.1, 8–853.3, 8–853.4, 8–853.5, 8–853.6, 8–853.7, 8–853.8, 8–853.x, 8–853.y, 8–854.2, 8–854.3, 8–854.4, 8–854.5, 8–854.6, 8–854.7, 8–854.8, 8–854.x, 8–854.y, 8–855.1, 8–855.3, 8–855.4, 8–855.5, 8–855.6, 8–855.7, 8–855.8, 8–855.x, 8–855.y, 8–856, 8-85a.0, 8-85a.1)
2020	R57.2 (septic shock) OR	
	At least one explicit sepsis code (see above)	AND R65.1 (SIRS with organ dysfunction) OR
	At least one explicit sepsis code (see above)	AND at least one ICD-10-GM code for organ dysfunction (see above) OR OPS code for organ dysfunction (see above) OR
	J09 OR J10 (laboratory confirmed Influenza) OR U07.1! (laboratory confirmed SARS-CoV2-infection)	AND at least one ICD-10-GM OR OPS code for organ dysfunction (see above)

*Abbreviations*: *ICD-10* International Classification of Diseases Version 10, German Modification, *OPS* German Procedure Classification, Operationen- und Prozedurenschlüssel

^a^codes were included in the definition if at least one hour of mechanical ventilation was documented in the course of the hospitalization

ICD-10-GM for sepsis codes were consistently defined by sepsis-1 definition [15] until the end of 2019. In 2020, sepsis coding was adjusted to the new sepsis-3 definitions [1]. To address these changes and to capture patients with viral sepsis, for which no explicit sepsis code is available since the change of the definitions, we extended our case identification strategies to cases with a code for Covid-19 or Influenza and a code indicating an acute organ dysfunction. The first hospital case of a patient with sepsis in the observation period is referred to as the index treatment; possible following sepsis cases are considered as recurrent sepsis. Only patients with continuous insured status 12 months before and 24 months (12 months for the 2020 patient cohort) after index treatment with sepsis or until death are included in the study.

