#### Sample size considerations

Based on preliminary studies using the same database and similar inclusion criteria, [4] we expect approximately 80,000 sepsis patients per year between 2016–2019. During the pandemic, the number of Non-Covid-19 sepsis patients may be lower, [16] but due to the inclusion of Covid-19 patients with organ dysfunction, we expect a similar number of patients to be included in our cohort in 2020. Patients with AOK insurance can receive treatment in any acute care hospital in Germany. According to a preliminary analysis, AOK-insured sepsis patients were treated in around 1650 hospitals of the 1900 German acute care hospitals between 2016–2020, thus our study will cover a large majority of German hospitals.

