#### Measurements

The module focuses on the three main points of the treatment pathway for sepsis patients: (A) pre-hospital care, (B) inpatient care, and (C) post-acute care.(A)Pre-hospital care: Pre-hospital health care utilization of patients with community-acquired sepsis in the 30 and 7 days prior to hospital admission is assessed. Specifically, contacts with the outpatient care system are analyzed, for example, how often the general practitioner, any outpatient specialist or the statutory health insurance emergency service were consulted, what laboratory or Point of Care Testing (POCT) diagnostics were performed, and if any initial anti-infective therapy was prescribed. For these outpatient contacts, the time latency between the last contact and the following inpatient admission with sepsis is assessed. Furthermore, we analyze which proportion of sepsis patients had pre-sepsis hospitalizations or emergency department visits, as well as which proportion of sepsis patients was admitted as emergency to their index treatment, and for which admission diagnosis.(B)Inpatient care: For the index hospitalization, we assess treatment characteristics, e.g. which organ replacement therapies were conducted, if patients received any immune absorbent therapy, if an intensive care complex or palliative care treatment was administered; as well as the departments involved in sepsis care. We identify inter-hospital transfers and characterize hospitals involved in the chain of sepsis care by the following key characteristics: type of hospital ownership (owned by local or federal state authorities, private for-profit organizations, or by voluntary charitable organizations or churches) number of hospital cases and beds, region (urban/rural), number of cases with (complex) intensive care complex treatment.(C)Post-acute care: Post-acute care utilization is assessed starting at the day of discharge from the last interhospital-transfer from the index hospitalization. We analyze long-term mortality, rehospitalizations (in general, for infectious diseases or recurring sepsis, for vaccine-preventable diseases, for ambulatory-care sensitive diagnosis), emergency department visits in hospitals or treatment by emergency services of the statutory health insurance emergency service, inpatient rehabilitation therapies, utilization of medical remedies, as well as outpatient consultations. We put special emphasis on the out-of-hospital intensive care and the conduction of long-term mechanical ventilation in that setting. Furthermore, psychotherapy and psychiatric medications are recorded and parameters concerning the return to work. Based on a detailed description of this post-acute sepsis care, we attempt to identify classes of health care utilization among sepsis survivors, examine whether such classes are constant or variable over time, and whether specific patient, sepsis, and treatment characteristics are associated with class membership.

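### Module 1: the index stay needs no sepsis-free interval, so 2016 index stays can be recurrences of 2015 sepsis, and the look-back for earlier sepsis lengthens by four years from the 2016 to the 2020 cohort

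*Protocol article*

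**What the plan says.** All places are in the protocol article, Module 1.

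- **Inclusion (Patient sample):** "Patients > 15 years of age with hospital-treated sepsis in 2016–2020 are included".
- **Index rule (Patient sample):** "The first hospital case of a patient with sepsis in the observation period is referred to as the index treatment". Of later stays it says: "possible following sepsis cases are considered as recurrent sepsis".
- **Pre-index condition (Patient sample):** "Only patients with continuous insured status 12 months before and 24 months (12 months for the 2020 patient cohort) after index treatment". Nothing is said about absence of sepsis in those 12 months.
- **Data held (Design and data source):** "The routine data from 2015–2021 are provided by AOK Research Institute (WIdO", with a patient ID that permits longitudinal linkage. One claims year therefore precedes the first inclusion year.
- **Expected numbers (Sample size considerations):** "we expect approximately 80,000 sepsis patients per year between 2016–2019". For 2020: "we expect a similar number of patients to be included in our cohort in 2020".

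The observation period is given no dates. Table 1 sets out the case definition for 2016–2019 and for 2020 only, so 2016–2020 is the natural reading. The limitations in the Discussion cover the 2020 coding change but not the unequal look-back.

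**The concern.** A first-in-period rule without a washout gives each index year a different sepsis history. A patient treated for sepsis in late 2015 and again in 2016 enters with the recurrence labelled as index. The same pair of stays one year later is labelled correctly. Survivors from 2016–2019 are also removed from later index cohorts, so the cohorts are increasingly restricted to first observed episodes.

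This reaches outputs that the plan names:

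- **Recurrent sepsis.** The post-acute outcomes include "rehospitalizations (in general, for infectious diseases or recurring sepsis, for vaccine-preventable diseases, for ambulatory-care sensitive diagnosis". In 2016, some stays counted as index already belong to that outcome.
- **New impairments after sepsis**, a planned subgroup. If the pre-index year contains sepsis, its sequelae count as pre-existing.
- **Covid-19 versus influenza versus others**, also a planned subgroup. Covid-19 cases, and cases that qualify by an influenza code, enter only under the 2020 definition and so carry the longest look-back. The other cases span all years.

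The drift runs alongside the 2020 change of case definition and the shorter 2020 follow-up. It would be hard to separate from them after the fact.

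**Working it through.** **Inputs from the article.** Inclusion years 2016–2020; claims 2015–2021; about 80,000 sepsis patients per year; in-hospital case fatality of 40% in Germany in 2016 (Background), hence 60% hospital survival.

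**Inputs assumed.** The article gives no recurrence rate. Its Background says only that survivors are often rehospitalized for causes that include sepsis. I take 5–15% of survivors with sepsis again in the following year, and I apply the 80,000 to 2015 as well.

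**Step 1. Look-back by index year.** If the period starts on 1 January of year *s*, an index stay in year *y* has between *y − s* and *y − s + 1* years of visible history.

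| Index year | Period 2016–2020 | Period 2015–2021 |
|---|---|---|
| 2016 | 0–1 year | 1–2 years |
| 2017 | 1–2 | 2–3 |
| 2018 | 2–3 | 3–4 |
| 2019 | 3–4 | 4–5 |
| 2020 | 4–5 | 5–6 |

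The gap between the 2016 and 2020 cohorts is four years on either reading. Carry-over from 2015 arises only on the first. On the second, the 2015 stay is itself the first case, and the 2016 stay is recurrent.

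**Step 2. Carry-over from 2015 into 2016 (first reading).**

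- Survivors of 2015 sepsis: 80,000 × 0.60 = 48,000.
- Recurrences in the following year: 48,000 × 0.05 = 2,400, up to 48,000 × 0.15 = 7,200.
- Share of 2016 index patients: 2,400 / 80,000 = 3%, up to 7,200 / 80,000 = 9%.

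These are upper values, because a recurrence within a year of 2015 sepsis can fall in 2015 itself.

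**Step 3. The annual count.** The figure of 80,000 comes from preliminary work on the same database. The article gives no inputs from which to rebuild it. To see what the first-case rule would do *if* 80,000 counts all sepsis patients in a year, let *h*₁ be the share of a year's patients who also had sepsis in the previous calendar year. Let that share fall by a factor *d* for each year further back. Then the number of index patients in 2020 is

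80,000 × [1 − *h*₁(1 + *d* + *d*² + *d*³)].

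The bracketed sum is 1.624 for *d* = 0.4 and 2.176 for *d* = 0.6.

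| Assumed *h*₁ | 2017 index patients, 80,000(1 − *h*₁) | 2020 index patients, *d* = 0.4 | 2020 index patients, *d* = 0.6 |
|---|---|---|---|
| 2% | 78,400 | 77,402 | 76,518 |
| 5% | 76,000 | 73,504 | 71,296 |
| 10% | 72,000 | 67,008 | 62,592 |

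The losses accumulate. At *h*₁ = 5% they are 4,000 in 2017 and 6,496 to 8,704 in 2020. A rolling 12-month look-back in every year would instead give a constant 80,000(1 − *h*₁), which is the 2017 column.

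**Step 4. Feasibility.** Every included patient must have been insured for the 12 months before index. A stay on 1 January 2016 needs claims back to January 2015, and these are held. The article says sepsis codes were consistently defined until the end of 2019, so the 2016–2019 code list can plausibly be applied to 2015.

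**The case against.** **The aim is descriptive.** The plan describes care pathways of sepsis patients, and including people with earlier sepsis is legitimate. No comparison by index year is named. This stands, but recurrence and the Covid-19 subgroup are named, and both depend on the sepsis history behind the index stay.

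**A washout is analysis-plan detail.** The article says that inclusion criteria are defined and analysis plans are prepared. A fuller document may contain a washout. Against this, the article states the index rule and the pre-index condition in full, and it leaves undated the one term on which they turn.

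**Some of the feared harm is small.** Pre-hospital utilization uses 30- and 7-day windows, so a 2015 sepsis could intrude only on index stays very early in 2016. This stands. For impairments, the 12 months of prior claims let recorded conditions be recognized as not new. That also stands, but a sequela of 2015 sepsis is then treated as background morbidity.

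**Stronger readings that the article does not support.**

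- A reader might infer that a 2020 index stay cannot follow any sepsis in 2016–2019. It cannot follow sepsis *identified in these claims*. Earlier episodes can be missed if the person was insured elsewhere more than 12 months before, if the episode was not coded (the Discussion concedes low sensitivity), or if it was influenza with organ dysfunction and no sepsis code, which Table 1 counts only for 2020.
- A reader might infer that a flat 80,000 per year is impossible under a first-case rule. The figure is approximate and rests on earlier work with similar criteria, which may already have counted first cases. No power or precision claim in Module 1 depends on it.

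**A washout on the first qualifying stay does not equalize the look-back.** This is correct: 2020 cases would still have 4–5 years of history. Only a rolling rule removes the inequality, and it lets one patient contribute several index stays with overlapping follow-up.

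**Conclusion.** The point holds as a defect of the stated index rule. On the natural reading of the observation period, some 2016 index stays are recurrences of 2015 sepsis that the held claims would reveal. On either reading, the look-back for earlier sepsis differs by four years between the 2016 and 2020 cohorts. That inequality follows from the definitions alone and needs no assumption about rates.

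The size of the carry-over is not derivable from the article. The 3–9% is an upper range. It rests on 60% hospital survival, 80,000 patients in 2015 as in later years, and an assumed 5–15% recurrence among survivors. The index counts for 2020 are illustrations that apply only if 80,000 means all sepsis patients in a year.

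Whole-cohort descriptions should be little affected. The concern is for recurrence rates, new impairments, and comparisons of Covid-19 with other sepsis.

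**What to change.** 1. Give the observation period start and end dates.
2. Define the index as the first qualifying stay in 2016–2020 with no qualifying sepsis stay in the preceding 12 months. For 2016, use the 2015 claims with the 2016–2019 code list. Join inter-hospital transfers into one episode before applying the flag. State whether a patient whose first stay fails the rule may enter with a later one.
3. For recurrence and for Covid-19 versus other comparisons, add a sensitivity analysis with the same rolling 12-month look-back in every index year. State how patients with more than one index stay are handled, since a sepsis stay at month 18 would be both an outcome and a new index. Step 2 alone removes the 2015 carry-over but leaves the look-back unequal.
4. State whether the approximately 80,000 per year counts index patients or all sepsis patients, and give the expected number under the final rule.
5. Mention the unequal look-back among the limitations.

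**Cost.** One flag computed from data already requested, a few percent fewer 2016 index patients, and one further sensitivity analysis that must allow for repeated stays per patient. No new data are needed.

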
For (A), (B) and (C), we examine health care costs from a payer perspective. All analyses will be conducted for the complete cohort of sepsis patients as well as for relevant subgroups, e.g. for patients stratified by age, sepsis focus, underlying pathogen (Covid-19 vs. Influenza vs. others), severity, region, underlying comorbidity, or patients with/without new impairments post-sepsis.

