#### Statistical analyses

We present descriptive analyses to describe the extent of health care utilization of different health services after sepsis and use visualization methods to map health care pathways among survivors, such as Sankey diagrams. Sankey diagrams are used to visualize patients’ pathways in terms of provider contacts after the sepsis event. This presentation allows us to detect patient flows after a hospital visit and provides support to define more detailed research questions [17]. Associations between hospital characteristics involved in the chain of hospital care and acute and long-term outcomes, as well as between treatment characteristics and the avoidance of (ambulatory-care sensitive) rehospitalizations are assessed by using appropriate regression models.

We attempt to describe the heterogeneity in health care utilization among sepsis survivors by Latent Class Analysis (LCA) modelling, which has proven as a promising tool to identify subgroups of patients with different patterns of health service use in previous research [18]. We will assess the stability of the class analysis over the follow-up period and study potential change in latent class membership by latent transition analysis (LTA) [19]. Additional analyses aim at explaining the heterogeneity in health care utilization by individual characteristics of the patients (e.g., age, sex, co-morbidities) and the sepsis (e.g., organ dysfunctions, duration of mechanical ventilation) by including these variables as predictors of the latent class membership in a multinomial logistic regression. Furthermore, the latent class membership may predict short and long-term outcomes, which can also be analyzed using regression based approaches with the latent classes as predictor of distal outcomes as described by Bakk and Kuha [20].

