#### Patient sample

(A) The patient sample includes all EMS cases treated by cooperating EMS organizations in Bayern and Baden-Württemberg between January 1, 2017, and December 31, 2021.

(B) The patient sample consists of individuals for whom a linkage can be established between PCR and health claims data. The health claims data cover the period from January 1, 2016, to December 31, 2022, thereby allowing for a one-year pre- or post-analysis of all patients' EMS-cases. The sample only includes data from individuals with a continuous insurance period or death within observation period.

In module 2, neither PCR nor health claims data are subject to sepsis-specific pre-selection. Consequently, the PCR comprise cases of patients with and without suspected sepsis, and the health claims database consists of patients with and without diagnosed sepsis.

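### Module 1 drops patients who leave the insurer alive after sepsis but keeps those who die, which can overstate mortality; require insurance before index only and censor afterwards

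*Protocol article*

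**What the plan says.** The eligibility rule is in the protocol article, Module 1, Patient sample: "Only patients with continuous insured status 12 months before and 24 months (12 months for the 2020 patient cohort) after index treatment with sepsis". The sentence goes on to make death the one exception: "after index treatment with sepsis or until death are included in the study". The rule governs entry to the study as a whole, not entry to one analysis.

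Under Measurements, Module 1 covers three phases: pre-hospital care, inpatient care and post-acute care. For the last, "We analyze long-term mortality, rehospitalizations" and other use are named. For all three phases, "we examine health care costs from a payer perspective". Under Statistical analyses, regressions on acute and long-term outcomes are planned, and "We attempt to describe the heterogeneity in health care utilization among sepsis survivors by Latent Class Analysis (LCA) modelling", followed by latent transition analysis. The claims data run from 2015 to 2021. On numbers, "we expect approximately 80,000 sepsis patients per year between 2016–2019".

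Module 2, Patient sample, part (B), has a rule of the same kind: "The sample only includes data from individuals with a continuous insurance period or death within observation period". Its Statistical analyses section plans Kaplan–Meier estimation of survival.

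The article describes no censoring at end of insurance for Module 1. The limitations in the Discussion mention selection through linkage in Module 2 and self-selection in Module 3, but not selection through the insurance rule.

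**The concern.** Whether a patient enters the cohort depends on what happens after index. Two patients with identical care up to month 6 are treated differently: if one dies then, the death counts; if the other changes insurer then, the patient and the six observed months disappear. The removals come only from people who were alive when they left, so they shrink the denominator of a mortality proportion without a matching loss of deaths, unless the leavers are themselves at high risk.

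Three things are at stake. First, in-hospital and long-term mortality, and the use and cost averaged over all patients, in which decedents become over-represented. Second, the pre-hospital and inpatient analyses, which need no coverage after discharge and are filtered by it all the same. Third, the comparison of 2020 with earlier years, because the filter runs for 12 months in one and 24 in the others. This is a stated inclusion criterion, so a later analysis plan cannot recover the patients if they are never extracted.

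**Working it through.** **Inputs from the article.** Required insurance after index: 24 months, or 12 for 2020. In-hospital case fatality: 40% (Background, Germany 2016). Expected patients: about 80,000 per year. There is no stated figure to reproduce for this point.

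**Inputs assumed.** The article gives neither a leaving rate nor a 24-month post-discharge mortality. I take a leaving rate *w* of 0.5–10% per year and a true post-discharge mortality *q* of 30–50%, with constant hazards and leaving independent of prognosis.

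**Formulae.** With T = 2 years, *d* = −ln(1−q)/2 and *c* = −ln(1−w):

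- deaths kept: A = d/(d+c) × (1 − exp(−(d+c)T))
- alive and still insured: B = exp(−(d+c)T)
- mortality under the rule: A/(A+B), against the true value *q*
- share removed: 1 − A − B

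**Worked case, q = 40%, w = 5%.** d = 0.2554 and c = 0.0513. B = 0.60 × 0.95² = 0.5415. A = (0.2554/0.3067) × 0.4585 = 0.3818. The rule gives 0.3818/0.9233 = 41.4%, and 7.7% of discharged patients are removed.

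**Excess in post-discharge 24-month mortality (percentage points):**

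| Leaving per year | q = 30% | q = 40% | q = 50% |
|---|---|---|---|
| 0.5% | 0.11 | 0.13 | 0.14 |
| 1% | 0.22 | 0.26 | 0.28 |
| 2% | 0.45 | 0.53 | 0.56 |
| 5% | 1.16 | 1.35 | 1.44 |
| 10% | 2.43 | 2.82 | 2.98 |

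**Counted from admission.** Take 40% in-hospital fatality and q = 40%, so the true total is 0.40 + 0.60 × 0.40 = 64.0%. At 5% leaving, the kept fraction is 0.40 + 0.60 × 0.9233 = 0.9540. In-hospital fatality then reads 0.40/0.9540 = 41.9%, and total mortality (0.40 + 0.60 × 0.3818)/0.9540 = 65.9%. At 2% leaving the two figures are 40.8% and 64.8%. Patients removed per 80,000: about 1,490 at 2% and 3,680 at 5%.

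**12- against 24-month rule.** With q = 40%, true 12-month mortality is 1 − √0.60 = 22.5%. At 5% leaving, deaths kept by month 12 are 0.2200. The 24-month rule gives 0.2200/0.9233 = 23.8%; the 12-month rule gives 0.2200/(0.2200 + 0.7359) = 23.0%. At 2% leaving they give 23.0% and 22.7%.

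**Does censoring repair it?** Simulation of 2 million patients, comparing the rule with Kaplan–Meier censored at end of insurance:

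| Scenario | Truth | Rule | Kaplan–Meier |
|---|---|---|---|
| Independent leaving, 2%/year | 40.0% | 40.5% | 40.0% |
| Independent leaving, 5%/year | 40.0% | 41.4% | 40.0% |
| 30% low-risk leaving at 10%, 70% high-risk at 1% | 40.0% | 41.9% | 40.7% |
| Same groups, leaving at 4% and 0.5% | 39.9% | 40.7% | 40.2% |

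(Low-risk and high-risk 24-month mortality: 15% and 50.7%.) Censoring restores the truth when leaving is independent and leaves part of the bias when it is not.

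**Can the direction reverse?** Yes. Let half the patients have 90% and half 10% mortality, so the truth is 50%, and let only the high-risk half leave, at hazard 0.05 per year. For that half, d = 1.1513, B = exp(−2.4026) = 0.0905 and A = 0.9584 × 0.9095 = 0.8717. The rule gives (0.8717 + 0.10)/(0.8717 + 0.0905 + 1) = 49.5%.

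**The case against.** The best defence is that complete follow-up suits the central post-acute analysis. Latent class and transition models over a fixed window are simplest with fully observed patients. The shorter window for 2020 follows from data ending in 2021 and is stated openly, and the 2020 cohort already differs through its case definition, which the Discussion acknowledges. The size of the effect is wholly assumed and is below one point for post-discharge mortality at 2% leaving or less. The study is non-interventional and largely descriptive. Censoring has an assumption of its own: if leavers differ in prognosis, it also leaves bias.

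Much of this stands. It justifies a complete-follow-up sub-cohort for the latent class work, and it limits what can be claimed about size and direction. It does not justify applying the same filter to mortality, all-patient cost, pre-hospital care and inpatient care. Nor is a bias of half a point negligible here: with 60% of 80,000 discharged alive, 48,000 patients, the standard error of a 40% proportion is √(0.24/48,000) = 0.22 points.

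In Module 2, a reader might infer that insurance is demanded for all of 2016–2022. The article does not support that: the sentence before the rule ties the data period to one year before or after each EMS case. The observation period is undefined, and no more than that can be said.

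**Conclusion.** The point holds for Module 1. The rule selects on post-index survival and insurance together. If leaving is unrelated to prognosis, or concentrated in low-risk patients, it overstates in-hospital and long-term mortality and tilts all-patient use and cost towards decedents. The differing window adds a small artificial gap between 2020 and earlier years, 0.8 points in 12-month mortality at an assumed 5% leaving. The excess in post-discharge mortality ranges from about 0.1 to 3.0 points over the assumed range and cannot be narrowed from the article.

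Four stronger readings go too far:

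- **Mortality must be overstated at every horizon.** Not so if leaving is concentrated in high-risk patients.
- **Survivor utilisation is biased.** For patients observed alive throughout, this needs leaving to be related to health or use, and the article says nothing about who leaves. A loss of younger, working patients from the return-to-work analysis is likewise undocumented.
- **The yearly cohorts are not comparable because of this rule.** The added difference is small.
- **Censoring alone cures the problem.** In the risk-related scenario it cut the bias from 1.9 to 0.7 points and did not remove it.

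**What to change.** In Module 1:

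- Require continuous insurance only for the 12 months before index. Follow every patient to death, end of insurance or end of data, and censor at end of insurance.
- Use Kaplan–Meier for death, Aalen–Johansen with death as competing event for rehospitalisation, and person-time rates or censoring-weighted means for use and cost.
- Where leaving relates to prognosis, adjust or use inverse-probability-of-censoring weights, for mortality as well as for use and cost.
- Report how many patients leave and how they differ from those who stay.
- Keep complete follow-up as a named sub-cohort for the latent class and transition analyses, and as a sensitivity analysis elsewhere.
- Add any remaining selection to the limitations.

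In Module 2, state that the insurance requirement is the 12 months before each EMS case and censor afterwards, in line with the Kaplan–Meier analysis already planned.

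The cost is a wider extraction filter at the same data source, revised plan wording, and time-to-event or weighted estimates in place of simple proportions. The Project timeline reports that inclusion criteria and analysis plans are settled and that ethics and data-protection votes are in hand, so the sponsor should check whether the wider filter needs an amended data request.
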